### Implementation strategies

The goal of SURE: CRC4D is to enable FQHC clinics to adopt strategies to optimize the use of evidence based colorectal cancer screenings (See Table 1) uptake for patients with type II diabetes. To accomplish this, multi-level, multi-component implementation strategies (see Table 3) will be utilized. The core components of this implementation effort includes the identification and engagement of 2–3 clinic change champions, who will participate in two virtual learning collaborative events [38–41] and lead the change effort in the clinic aided by bi-weekly virtual practice facilitator support [38, 42–49]. The SURE: CRC4D toolkit will include guidance on pulling data to develop and implement quality monitoring systems to provide regular audit/feedback to the clinic, patient educational materials in English and Spanish and dissemination materials for clinical meetings to orient other clinic members to the change process being implemented to optimize CRC screening for patients with diabetes [50, 51]. Clinic champions will tailor toolkit resources as clinics may have different electronic medical records, type and composition of staff, clinical workflows, and standing clinical team meetings.

**Table 3 Tab3:** Timeline for implementation activities & assessment

Single Group	Year in months											
**Implementation Activities**	1	2	3	4	5	6	7	8	9	10	11	12
Identify clinical champions	x											
Learning collaborative	x		x									
Virtual Practice facilitation	x	x	x									
Patient Education Materials	x											
Clinical Meeting Materials	x	x										
Quality Monitoring System	x	x	x	x								
**Assessments**												
EHR abstraction	x											x
Clinic Staff and Clinician Qualitative Interviews	x	x	x			x						x
Practice Information Form	x					x						x
Clinic Staff and Clinician Questionnaires	x					x						x

The implementation will be rolled out over a 12-week period. Initially, clinics will be asked to identify 1–3 clinic champions, with at least one clinician (i.e., physician, advanced practice nurse, physician assistant) per team. Each team will meet with the external practice change facilitator approximately two weeks prior to the initial learning collaborative. This initial facilitation meeting is introductory, with the goal of encouraging clinic champions to reflect about the current clinic CRC screening strategies and diabetes care management processes prior to the 1st virtual learning collaborative. Clinical champions will attend the 1- hour virtual learning collaborative, where the materials in the SURE: CRC4D toolkit will be provided and reviewed, and each clinic team will formulate practice change goals. Teams will decide on how to deploy the toolkit strategies at their FQHC sites over the course of the next ten weeks. The practice facilitator will support the clinic champion team in the development, implementation, and refinement of the local practice change plan. The champions will meet with the practice facilitator every two weeks for 8 weeks (4 times). During this time, the plan will be refined and adjusted based on feedback from clinic leaders and practice staff members and identified strengths and barriers that are encountered during the implementation effort. At week 10, a second learning collaborative will be virtually convened, providing a forum where the different clinic teams can share their successes and obstacles during the development and execution of their plan. This forum will foster cross-team learning and idea generation that can inform the refinement of the SURE: CRC4D toolkit and sustainability of practice change efforts. Two weeks after the second learning collaborative, a final virtual facilitation meeting will be held to reflect and refine the practice plan to support sustainability.

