### Conceptual framework

The design of this study was guided by the EPIS framework. EPIS is an evidence-based practice (EBP) implementation framework that includes four defined phases for assessment of inner and outer contextual factors that influence EBP implementation (see Table 2). For this study, the EBP is CRC screening uptake among age eligible patients with diabetes. Exploration is the act of identifying patient needs and the availability of EBPs to address identified needs, and the decision to adopt evidence into practice based on fit within the inner clinical context. During this phase, the adaptations to the evidence are based on system, organization, and individual patient factors. Preparation includes planning implementation, inventorying proposed challenges, and developing strategies to overcome anticipated barriers. A critical component of this phase is the planning of implementation strategies to support EBP utilization in the next two phases and to address organizational climate to ensure that EBPs will be supported, expected, and rewarded. During the clinical trial, this study focuses on implementation, the process of assuring and balancing fidelity to the EBP delivered with adaptations needed to assure program success. Sustainment focuses on maintenance and program and factors impacting implementation over the long haul. EPIS considers innovation factors, which are the characteristics of the EBP being implemented. The innovation-EBP fit considers if the EBP fits the patient, provider, and organizational needs. Innovation factors are assessed and can be adapted to maximize the fit of an EBP while maintaining the core elements of the intervention to retain fidelity.

**Table 2 Tab2:** EPIS constructs for implementation of SURE: CRC4D toolkit to promote screening in patients with diabetes

Domains	Inner context	Outer context
Actors	Decision makers, Champions, Adopters, Staff	Patients, Policymakers/Advocates, Funders
Resources	Electronic Health Record, Materials, Supports	Referral for CRC screen; Patient Navigation; Community Organizations
EBP	Core elements for fidelity; EBP fit with Organization	EBP fit with practice; Practice Incentives

Acronyms: EBP: evidence-based practice, CRC: colorectal cancer screening

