### Methods

#### Study participants and setting

This single arm trial will be conducted in six FQHC clinical sites in New Jersey. Eligibility criteria for the FQHC clinics include: (1) provide care to at least 450 patients aged 50–74 years; (2) 10% of patient population previously diagnosed with diabetes; (3) located in New Jersey; and, 3) clinical and administrative leadership willing to engage in the intervention and research requirements (interviews, data validation, process evaluation). Implementation outcomes will be assessed using mixed methods guided by the EPIS constructs (see Table 2). The methods of this study have been reported using Standard Protocol Items: Recommendation for Interventional Trials (SPIRIT) guidelines (Supplemental file 1).

During the implementation a clinic-based registry of patients eligible for CRC screening will be developed for each clinic at baseline and updated at six and 12 months post-baseline. Patient eligibility criteria will include: (1) patients not up-to-date or due for CRC screening [4]. based on electronic health record (EHR) documentation (e.g. FOBT/FIT test in last year, flexible sigmoidoscopy within 4 years, or colonoscopy within 9 years), (2) previous diagnosis of type II diabetes, (3) age-eligible for CRC screening (45–74 years of age) and (4) ) FIT/FOBT that has been ordered for more than 6 months that has not been completed or a sigmoidoscopy or colonoscopy referral that has not been completed for 12 or more months. Patients are excluded if they have EHR documentation medical conditions not concordant with standard CRC screening intervals (e.g. prior CRC diagnosis, inflammatory bowel disease, renal failure, etc.) [4].

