**Implementation Outcomes***	
Patient Acceptability	QUANT
Staff/Clinician Fidelity	QUANT
Staff/Clinician Acceptability	QUAL
Feasibility	QUAL

*Note* * These assessments will be collected from the electronic health record in aggregate at baseline and 12 months post implementation; QUANT = quantitative; QUAL = qualitative

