### Patient level: clinical effectiveness outcome and implementation assessment

The primary outcome variables to assess clinical effectiveness will be the clinic level proportion of patients with diabetes who: (a) receive any CRC screening and (b) complete a colonoscopy at 12 months from baseline. An exploratory analysis will assess clinic-level CRC screening completion by glucose control (controlled vs. uncontrolled, i.e., HbA1c > 9 at 12 months). Patient level data is collected in aggregate and will include no identified personal health information.

Patient acceptability will be assessed through the assessment of patient rates of opting-out and non-adherence of CRC screening. This rate will be based on the proportion of CRC screening among patients with diabetes compared to overall eligible patient population (without diabetes) in each clinic.

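### The final EHR pull falls in the month the 12-month outcome window closes, with no later pull, so referral procedures reported late may be misclassified

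*Protocol article*

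**What the plan says.** All references are to the protocol article.

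- **Timing of the pull.** In Table 3 the row "EHR abstraction" is marked in months 1 and 12 and nowhere else. Under Study participants and setting, the clinic registry is built at baseline and "updated at six and 12 months post-baseline".
- **Outcome window.** The section on the patient-level effectiveness outcome defines the colonoscopy outcome as the clinic-level proportion of patients with diabetes who "complete a colonoscopy at 12 months from baseline"; any screening is the other primary outcome.
- **Source.** The note under Table 4 says "These assessments will be collected from the electronic health record in aggregate at baseline and 12 months post implementation". No other source for the clinical outcomes is named.
- **How the tests are obtained.** Table 2 lists "Referral for CRC screen; Patient Navigation; Community Organizations" as outer-context resources. The patient eligibility criteria refer to "a sigmoidoscopy or colonoscopy referral that has not been completed for 12 or more months" and, for stool tests, "FIT/FOBT that has been ordered for more than 6 months that has not been completed".
- **Start of the intervention.** "The implementation will be rolled out over a 12-week period"; Table 3 marks the quality monitoring system through month 4.
- **Success rules.** Quantitative analysis sets 25% for any screening and 15% for colonoscopy or flexible sigmoidoscopy, both among those unscreened.

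**The concern.** An outcome taken from a clinic record is complete only once the reports for the whole window have arrived. Here the record is read in the month the window ends. Procedures that follow a referral reach the clinic's record as a report, and for those done in the last weeks the report may still be outstanding. With a 12-week roll-out at the start of the year, procedures prompted by the intervention tend to fall in the later part of the window, where this matters most.

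The trial has a single arm and judges success against fixed percentages, so incomplete capture is not offset by the same incompleteness in a comparison group. Data are collected in aggregate, so late reports cannot be added patient by patient to figures already supplied; they need another pull. Clinics may also use different record systems, so completeness could vary by site.

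The same delay acts at the start. A patient whose colonoscopy was done shortly before baseline but not yet reported looks unscreened. When the report arrives during follow-up, it can be counted as a success unless the date of the procedure is checked.

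**Working it through.** **Inputs from the article.** 50 patients with diabetes per clinic, 40% already up to date, six clinics (Power calculations); thresholds of 15% and 25% (Quantitative analysis); 12-week roll-out and a quality monitoring row ending in month 4 (text and Table 3).

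**Assumptions, not in the article.** Reporting lag L of 0.5 to 2 months; procedures spread evenly over the last T months before the pull; pull at the end of the window; every report still outstanding at the pull is missed. T = 12 spreads them over the whole year, T = 9 starts after the roll-out, and T = 8 starts after month 4.

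**Step 1: the plan's own sample size.** 50 × (1 − 0.40) = 30 per clinic; 30 × 6 = 180. This reproduces the stated target.

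**Step 2: observed rate at a true 15%.** 0.15 × 180 = 27 completed procedures. Share missed = L/T; seen = 27 × (1 − L/T); observed rate = seen/180.

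| T (months) | L (months) | Share missed | Seen | Observed rate |
|---|---|---|---|---|
| 12 | 0.5 | 4.2% | 25.9 | 14.4% |
| 12 | 1 | 8.3% | 24.8 | 13.8% |
| 12 | 2 | 16.7% | 22.5 | 12.5% |
| 9 | 0.5 | 5.6% | 25.5 | 14.2% |
| 9 | 1 | 11.1% | 24.0 | 13.3% |
| 9 | 2 | 22.2% | 21.0 | 11.7% |
| 8 | 2 | 25.0% | 20.25 | 11.3% |

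If only half of the late reports are outstanding, each loss halves.

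**Step 3: any screening.** Take a true 25% of which 15 points are colonoscopy. With L = 1 it reads 25 − 15 × 1/12 = 23.8% (T = 12) or 25 − 15 × 1/9 = 23.3% (T = 9). The loss in points equals that for colonoscopy, but it is a smaller share of the rate.

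**Step 4: against the precision of the trial.** The 80% confidence interval half-width at 15%, ignoring clustering, is 1.2816 × √(0.15 × 0.85/180) = 3.4 points. A one-month lag costs 1.3 points (T = 12) to 1.7 points (T = 9), about half of that or less.

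**Step 5: against the threshold.** Reading the 15% rule as at least 27 of 180, with independent patients and L = 1:

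| True rate | Full capture | T = 12 | T = 9 |
|---|---|---|---|
| 15% | 0.53 | 0.34 | 0.29 |
| 20% | 0.97 | 0.90 | 0.86 |

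**Step 6: the opposite error.** If procedures are counted by when they appear in the record, roughly L months' worth of pre-baseline procedures enter as false successes while L months' worth at the end drop out. The net error is about L × (monthly number before baseline − monthly number at the end of the window). The article gives neither number, so the sign cannot be derived from it. Steps 2 to 5 show the end-of-window error alone.

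**The case against.** The strongest reply is that a journal article commonly leaves the extraction date, data cut-off and handling of late reports to the full protocol. A mark in month 12 of a month-level grid does not fix a date, and nothing says late reports are discarded. Clinics must also agree to data validation, whose content is not described. This stands as a reason for modest weight. It does not remove the point, because months 1 and 12 are a stated schedule and the registry has no update after month 12.

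A reader might go further and infer that late colonoscopies are lost, and that the colonoscopy rate is therefore biased downward relative to stool tests done in the clinic. The article does not support that. It gives no reporting lag, does not say where endoscopy is performed, and does not say that stool tests are processed or tracked in the clinic; they too can have return and laboratory delay. The 12 months in the eligibility criteria is the time a referral has stood uncompleted, not a reporting time, and stool tests have a similar rule at more than 6 months. Late baseline reports push the other way.

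It may also be said that the note under Table 4 places the assessment 12 months after implementation. Counted from the end of the 12-week roll-out, that is about month 15, which would already allow a run-out if the window closes at month 12. But Table 3 stops at month 12 and the outcome definition counts from baseline, so this wording adds an ambiguity and does not settle the matter.

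**Conclusion.** The point holds as a low-cost improvement, not as a demonstrated error. The documents establish a final pull in the closing month of the window, no later pull, a single stated source and procedures that depend on referral. On that schedule, late-reported colonoscopies and sigmoidoscopies may be missed at the end, and pre-baseline ones may be miscounted as successes.

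The size is unknown. Under the assumptions above, a true 15% would be observed at about 14.4% to 11.3% for lags of 0.5 to 2 months, and closer to 15% if only some reports are late. For lags up to about a month the shift is small against the 80% interval and matters mainly when the true rate lies near 15%. Both primary outcomes and the 15% criterion are exposed. A certain net downward bias, or a known difference between test types, cannot be claimed.

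**What to change.** 1. State one outcome date, reconciling 12 months from baseline (outcome definition, Table 3) with 12 months post implementation (Abstract, Table 4 and its note).
2. Schedule the final EHR abstraction about 2 to 3 months after that date, and add it to Table 3.
3. Count only tests whose service date falls inside the window, whenever the report arrived.
4. Correct baseline status by service date in the same way, so that a patient screened before baseline but reported later is not treated as unscreened.

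The cost is a read-out 2 to 3 months later. No additional patients or visits are needed, and the outcome window keeps its length.

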### Evaluation of the effectiveness and implementation of SURE: CRC4D

The effectiveness and implementation of SURE: CRC4D will be evaluated using a mixed method learning evaluation strategy, where ongoing data collection and analysis are used to refine implementation to optimize adoption of CRC screening for patients with diabetes [52, 53]. This evaluation is designed to address two research questions: (1) are the adapted implementation strategies clinically effective in increasing CRC screening rates for patients with diabetes; and, (2) are the implementation strategies feasible and acceptable to implementers (e.g., clinicians and staff) and patients in FQHCs? This evaluation builds an evidence base about the effectiveness of the implementation strategies in a real-world context and allows for the collection of data that can be used to refine the implementation toolkit for a larger scale, definitive cluster randomized controlled trial. Guided by EPIS, contextual factors were selected based on suggestions from clinical stakeholders, community partners, and previous literature suggesting they may influence implementation success [54–56] (see Table 4). The following assessments and measures will be collected to evaluate the trial:

**Table 4 Tab4:** Study measures

	Baseline & 12-month post implementation
**Effectiveness: Clinic Level Patient Outcomes***	
Demographics	QUANT
Glycemic Control (HgbA1C < 9)	QUANT
Any CRC screening/patients eligible	QUANT
Colonoscopy completion/patients eligible	QUANT
CRC rate by glycemic control	QUANT
**Contextual Factors: Clinic and Clinic Team-Level Variables**	
Implementation Climate/History of Implementation^36^	QUANT
Change Process Capability	QUANT
Adaptive Reserve	QUANT
Medical Provider/Staff Demographics (e.g., age, sex, race, training, years in practice)	QUANT
Facility Resources	QUANT/QUAL
Organizational Readiness for Change^84^	QUANT/QUAL
Implementation Leadership Scale/Leadership Style	QUANT/QUAL
**Implementation Outcomes***	
Patient Acceptability	QUANT
Staff/Clinician Fidelity	QUANT
Staff/Clinician Acceptability	QUAL
Feasibility	QUAL

*Note* * These assessments will be collected from the electronic health record in aggregate at baseline and 12 months post implementation; QUANT = quantitative; QUAL = qualitative

### Organizational assessments

Guided by EPIS, contextual factors will be evaluated at baseline and 1 year-post implementation. Medical Directors or the Chief Operating Officer of each clinic will be asked to complete a web-based survey called the Clinic Organizational Information Form (COIF). This survey assesses *Implementation Climate* and *History of Implementation* related to CRC screening and diabetes management [35]. Additionally, patient demographics, management strategies, and payor mix are collected using this survey for each clinic.

### Clinic staff measures and assessments

The Clinic Staff Questionnaire (CSQ) will be administered to all practice clinicians and staff members at baseline and 12-month post-implementation. The clinic team measures include *Medical Provider and Staff Background* and history with the organization. Additionally, *Change Process Capability* will be measured, specifically “previous history of change,” and “ability to initiate and sustain change.” [57]. These two measures have been identified these as key mechanisms for successful organizational change and its wide use in cardiovascular care implementation [58–60]. Additional practice-based measures will include: *Adaptive Reserve* a feature of resilient organizations shown to be associated with practice-level implementation of CRC screening, will be measured in the CSQ with the validated 23-item scale [57, 61]. The CSQ will also include the *Implementation Leadership Scale* (ILS), a brief psychometrically strong measure that contains 12-items with four subscales of proactive, knowledgeable, supportive, and perseverant leadership [62].

### Process data outcomes

Learning collaborative and facilitation phone calls will be audio recorded and transcribed to document issues that arose during the implementation process. Additionally, qualitative interviews will be conducted at baseline and beginning at 6 months post implementation. We will select key implementers (3–4 individuals per site) to assess perceptions of organizational readiness to change, leadership style and additional facility characteristics (e.g., assets and deficits of location, satisfaction with ease of access to facility, etc.). Staff and clinician perceptions of the SURE: CRC4D implementations’ feasibility and acceptability will also assessed asking providers and staff to describe their implementation experiences. The interviews will probe stakeholder perceptions of change in their organizations, systems, and factors that they think impacted implementation. Staff or provider fidelity will be assessed based on the clinic-level proportion of eligible patients who were (1) contacted based on implementation protocol and (2) completed any CRC screening at 1 year.

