**Methods:**

Guided by the Exploration, Preparation, Implementation and Sustainment Framework, we conducted a stakeholder-engaged process to identify multi-level change objectives for implementing optimized CRC screening for patients with diabetes in FQHCs. To identify change objectives, an implementation planning group of stakeholders from FQHCs, safety-net screening programs, and policy implementers were assembled and met over a 7-month period. Depth interviews (*n* = 18–20) with key implementation actors were conducted to identify and refine the materials, methods and strategies needed to support an implementation plan across different FQHC contexts. The planning group endorsed the following multi-component implementation strategies: identifying clinic champions, development/distribution of patient educational materials, developing and implementing quality monitoring systems, and convening clinical meetings. To support clinic champions during the initial implementation phase, two learning collaboratives and bi-weekly virtual facilitation will be provided. In single group, hybrid type 2 effectiveness-implementation trial, we will implement and evaluate these strategies in a in six safety net clinics (*n* = 30 patients with diabetes per site). The primary clinical outcomes are: (1) clinic-level colonoscopy uptake and (2) overall CRC screening rates for patients with diabetes assessed at baseline and 12-months post-implementation. Implementation outcomes include provider and staff fidelity to the implementation plan, patient acceptability, and feasibility will be assessed at baseline and 12-months post-implementation.

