Guided by the insights of the exploration and preparation phases, we developed the Strategic Use of Resources for Enhanced ColoRectal Cancer Screening in Patients with Diabetes (SURE: CRC4D) implementation toolkit, which includes tailorable materials and protocols that will be tested in a single arm, hybrid type 2 effectiveness-implementation single arm clinical trial. The objectives of this trial are to:

Determine the effectiveness of the SURE: CRC4D multi-component implementation strategies to increase CRC screening uptake among patients with diabetes.Evaluate the fidelity, feasibility, and acceptability of SURE: CRC4D implementation.Refine the SURE: CRC4D toolkit based on multi-level user feedback and conduct an evaluation to promote scalability and sustainable use.

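### Fidelity is defined by patients contacted and patients screened, so it does not directly count delivery of the SURE: CRC4D strategies, half of it repeats a primary outcome, and its baseline time point has nothing to measure

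*Protocol article*

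**What the plan says.** **Target.** The second trial objective is "Evaluate the fidelity, feasibility, and acceptability of SURE: CRC4D implementation". The abstract states both the target and the timing: "Implementation outcomes include provider and staff fidelity to the implementation plan, patient acceptability, and feasibility will be assessed at baseline and 12-months post-implementation".

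**Strategies.** The abstract lists the endorsed strategies as "identifying clinic champions, development/distribution of patient educational materials, developing and implementing quality monitoring systems, and convening clinical meetings", supported by two learning collaboratives and bi-weekly facilitation. Table 3 (Implementation strategies) sets these out as six activities: champions, learning collaboratives, practice facilitation, patient education materials, clinical meeting materials and a quality monitoring system. Clinics adapt them locally: "Clinic champions will tailor toolkit resources as clinics may have different electronic medical records, type and composition of staff, clinical workflows".

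**Measure.** Process data outcomes gives the definition: "Staff or provider fidelity will be assessed based on the clinic-level proportion of eligible patients who were (1) contacted based on implementation protocol". The two items together read "1) contacted based on implementation protocol and (2) completed any CRC screening at 1 year".

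**Source and timing.** Table 4 lists staff and clinician fidelity as a quantitative implementation outcome. Its note says "These assessments will be collected from the electronic health record in aggregate at baseline and 12 months post implementation".

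**The concern.** The stated target is delivery of a set of clinic-level strategies. The stated measure is built from what happened to patients. A clinic's fidelity score should rise when its champions are in place, its team attends the collaboratives, its facilitation meetings take place and its monitoring runs. Nothing in the definition makes it do so.

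This matters because the trial has one arm and six clinics, and its results are meant to refine the toolkit for a definitive cluster randomized trial. If screening does not rise, the team must know whether the strategies failed or were never put in place. If it does rise, the team must know which strategies were actually running. A fidelity score that is partly the screening rate itself cannot answer either question.

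The timing raises a second problem. A baseline value of adherence to a plan that a clinic does not yet have cannot be interpreted.

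**Working it through.** No sample size or error rate bears on this point. The check sets the definition beside the strategies, the primary outcome and the timeline.

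**1. Fidelity items against the Table 3 activities**

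| Table 3 activity | Item 1: eligible patients contacted | Item 2: any CRC screening completed at 1 year |
|---|---|---|
| Clinical champions identified | not counted | not counted |
| Learning collaboratives | not counted | not counted |
| Practice facilitation | not counted | not counted |
| Patient education materials | at most indirectly, if they reach patients through a contact | not counted |
| Clinical meeting materials | not counted | not counted |
| Quality monitoring system | at most indirectly, if it prompts or records a contact | not counted |

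Directly counted: 0 of 6. The two indirect entries are judgements, because the article does not define a contact.

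**2. Item 2 against the primary outcome**

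- Fidelity item 2 is the clinic-level proportion of eligible patients who completed any CRC screening at 1 year.
- Primary outcome (a), in the section on patient-level effectiveness, is the clinic-level proportion of patients with diabetes who receive any CRC screening at 12 months. Table 4 gives its denominator as eligible patients.

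These are the same event at the same time, so 1 of the 2 fidelity items is an effectiveness outcome.

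The sentence could also mean one proportion of patients who meet both conditions. That proportion cannot exceed the screening proportion. A clinic exactly at the 25% success threshold in Quantitative analysis could then score at most 25% on fidelity, even with every eligible patient contacted and every strategy delivered. The conclusion holds on either reading.

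**3. Timing**

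- The abstract, and the header and note of Table 4, place fidelity at baseline and 12 months.
- The text under Table 3 says the toolkit is provided, and each team formulates its goals, at the first learning collaborative. Before that there is one introductory facilitation meeting.
- Process data outcomes mentions only 1 year.

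At baseline, then, there is no clinic plan to follow, and the general timing does not fit the specific definition.

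**4. What a delivery score could count**

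The text under Table 3 describes one introductory facilitation meeting, four bi-weekly meetings over 8 weeks, and one final meeting. Read as separate meetings, that is 1 + 4 + 1 = 6 planned per clinic. Two collaboratives are planned. The final meeting comes two weeks after the second collaborative at week 10, so at week 10 + 2 = 12. The collaborative and facilitation calls are recorded and transcribed, but the stated purpose is to document issues that arose, not to score delivery.

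**The case against.** The strongest reply is that patient contact may well be part of the plan. The definition ties contact to the implementation protocol, the toolkit is said to contain protocols that the article does not reproduce, distribution of patient materials is a named strategy, and a registry of eligible patients is built at each clinic. This stands. A reader might infer from Table 3 that the measure scores an act the plan never prescribes, but the article does not establish that. A reader might also infer that a clinic delivering everything could score near zero, or one delivering almost nothing near 100%. Those cases are hypothetical, because contact is not defined.

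A second reply is that Conceptual framework speaks of fidelity to the evidence-based practice, which it identifies as CRC screening uptake. Contact and completion fit that sense better. This explains how the definition may have arisen. It does not reconcile it with the abstract and the objective, which name the implementation plan and SURE: CRC4D.

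A third reply is that the baseline listing is loose drafting. The abstract sentence pools several outcomes. The Table 4 note covers a whole block, including qualitative feasibility and staff acceptability, which the text obtains from interviews rather than from the health record. That is fair. A reader might infer that a baseline-to-12-month change in fidelity will be tested, but no such analysis is stated. What remains is an inconsistency to be corrected.

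Finally, fidelity is not the only evidence on delivery. Recorded calls, interviews with key implementers and quarterly comparative case analysis will all inform it. None of these is stated as a fidelity measure.

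**Conclusion.** The point holds as a mismatch between a stated target and a stated definition. Fidelity to the implementation plan is measured by two patient-level proportions. Together they directly count none of the six listed activities, and one of them is the same event as primary outcome (a). As defined, fidelity cannot distinguish non-delivery from ineffective strategies. The baseline time point in the abstract and Table 4 has no interpretable content and does not fit the 1-year wording of the definition.

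This is not a detail that an article may leave to a fuller document: the article gives the definition, and it conflicts with the article's own account of what fidelity is. The conclusion does not depend on whether contact is prescribed. If it is, the measure still leaves the other listed strategies without a direct count. The primary effectiveness analysis is unaffected. What suffers is its interpretation, the fidelity objective and the refinement of the toolkit. The change should be made.

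**What to change.** Define fidelity as a per-clinic delivery score taken after roll-out, with one item for each Table 3 component:

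- champion team in place, with at least one clinician (the article gives both 2–3 and 1–3 champions, so settle the number first);
- learning collaboratives attended, out of 2;
- facilitation meetings held, out of those planned (6 on the reading above);
- quality-monitoring report set up;
- clinical meeting held;
- patient materials in use.

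Abstract the items from the recorded collaborative and facilitation calls. Some items may not appear there, notably quality monitoring, which Table 3 runs to month 4 while the calls end at about week 12. Ask about these in the existing calls, or in the interviews that begin at 6 months.

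Report the proportion of eligible patients contacted as a separate process measure, with contact defined. Take screening completion out of fidelity and leave it as primary outcome (a). Remove the baseline time point for fidelity from the abstract and Table 4, and change the Table 4 note so that the health record is not given as the source for this row. State whether fidelity refers to the plan or to the evidence-based practice.

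The cost is a change of wording, a short checklist, modest abstraction of existing recordings for six clinics, and a few added questions. No new visits are needed.
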